#### Setting

The exercise training sessions will be carried out at the facilities at CFAS and at the Department of Physical and Occupational Therapy, Copenhagen University Hospital, Hvidovre.

The participants in the control group are instructed to continue their life unchanged and will receive a standard of care in the healthcare system. Standard of care or usual care includes yearly or half-yearly visits to the Department of Infectious Diseases for control of their chronic viral disease with blood tests, fibroscan, and consultation with doctors and nurses. Also, any other treatment participants receive for any other chronic or acute disease at their general practitioner or outpatient clinic. No diet or exercise intervention is offered to the control group.

### Criteria for discontinuing or modifying allocated interventions {11b}

The participants will be randomly allocated to a group (control /exercise) after the initial baseline test is performed. Sufficient compliance to the exercise intervention is defined by the compliance criteria: Completing ≥ 70% of the 36 exercise training sessions with ≥ 50% of the assigned heart rate max (HR_max_). No participant will be allocated to a different arm after randomization. If a participant is given hepatic steatosis-inducing medicine or diagnosed with HIV/hepatitis C during the trial, they will be taken out of the trial.

### Strategies to improve adherence to interventions {11c}

Participants in the exercise group will be monitored doing the intervention by a trainer and encouraged to perform according to guidelines. If a participant does not comply with the prescribed exercise training in two connecting sessions, the primary investigator will be informed, and the participant will be contacted to identify the challenges and find a solution with the participant to improve adherence.

### Relevant concomitant care permitted or prohibited during the trial {11d}

All concomitant care is allowed during the trial.

### Provisions for post-trial care {30}

All patients will receive unchanged standard medical care by the Danish public health care system. If any clinically relevant findings occur during the trial the participant will be referred to the relevant department for clarification and treatment. All participants will be covered by The Danish Patient Insurance Association for any injury that may occur as a direct consequence of trial-related procedures.

### Outcomes {12}

#### Primary outcome assessed at week 13 after randomization

The primary outcome is the fat fraction of the liver (%). A fat fraction > 5% is considered hepatic steatosis; having hepatic steatosis is considered a risk factor for the development of hepatocellular carcinoma [9, 15]. Thus, a normalization of the fat fraction in the liver < 5% would be considered a risk reduction.

The primary outcome is assessed by MRI measurements of the proton density fat fraction [59, 60] (1.5 Tesla field strength GE Signa Artist-scanner. IDEAL-IQ sequence).

#### Secondary outcomes assessed at week 13 after randomization

Hepatokine secretion during a somatostatin and glucagon hormone infusion (ANGPTL-4, follistatin, GDF15, FGF-21)Cytokine secretion during a hormone infusion (IL-6, IFN-γ, TNF-α, IL-1β, IL-4, IL-8, IL-10)Measurement of visceral fat (kg) based on Dixon MRI of the abdomenBody composition (fat and lean mass (kg)) assessed by dual-energy X-ray absorptiometry (DXA) scansMeasurement of body weight (kg), height (cm), hip and waist circumference (cm) calculating body mass index (kg/m^2^) and waist to height ratioBlood pressure measurements (systolic (mmHg) and diastolic (mmHg))Physical fitness by VO2_max_ (mL/kg/min) performed on ergometer bikesPhysical activity monitoring is assessed by how many hours a participant is sedentary or active (hours: minutes/week) measured by the use of accelerometers AX3 axivityOGTT measurements (glucose (mmol/L), insulin (pmol/L), c-peptide (pmol/L)): the amount of normal OGTT (%) and mathematical modelling of endocrine pancreas alpha and beta-cell function and insulin resistance.Liver blood samples (ALT(U/L), AST(U/L), FIB-4, INR, and hepatitis B viral load)Blood samples (CRP (mg/L), HbA1c (mmol/mL) and lipids (total cholesterol (mmol/L), total triglyceride (mmol/L), low density lipoprotein (LDL) (mmol/L), high-density lipoprotein (HDL) (mmol/L))Nail fold capillary assessment of vascularity (findings of the following: CD: Capillary Density-Distribution, CE: Capillary Enlargement, CT: Capillary Tortuosity, BC: Branching of the Capillaries, MH: Microhemorrhage, AA: Avascular Area, SH: Splinter Hemorrhage)Fibroscan measurements of hepatic steatosis and liver fibrosis (CAP (dB/m), fibrosis = TE-score (kPa))IPAQ-SF (participants self-assessed scoring of physical activity the previous 7 days resulting in a calculation of Metabolic Equivalence of Task (MET)-minutes)IQOLA SF-36: Quality of life questionnaire at baseline and post the intervention (participants self-assessed scoring of eight health concepts ranging from 0 to 100: physical functioning, role limitations due to physical health problems, role limitations due to personal or emotional problems, energy/fatigue, emotional well-being, social functioning, pain, and general health perception) at baseline to post-intervention24-h recall food registration assessed by changes in amount and change of food divided into food categories and amounts of each categoryLiver biopsies change in the description of the degree of steatosis and liver inflammation

### Participant timeline {13}

[figure not shown]

### Sample size {14}

The sample size for the primary outcome was calculated in relation to the fat fraction of the liver. To our knowledge, no-exercise intervention studies have been performed in patients with CHB. We used exercise training intervention studies in non-alcoholic-fatty liver disease (NAFLD) or sedentary, dysglycemic patients with measurements of MRI measurements of intrahepatic lipid content as the fat fraction to calculate the sample size. The one-sided test is chosen due to the current literature, which states that exercise training intervention generally reduces the fat fraction of the liver and does not increase the fat fraction of the liver [36, 61–63]. Assuming a SD of − 2,6 [36] and no change in the control group. An 80% chance of detecting a − 2.8% between-group change in liver fat fraction with a one-sided 0.05 significance requires *n* = 14 in each group.

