### Trial design {8}

This is an investigator-initiated trial that was registered at www.ClinicalTrials.gov before inclusion of the first participant. The trial is designed as a block-randomized, controlled, unblinded, clinical, superiority, exploratory, intervention trial. Thirty persons with CHB and hepatic steatosis are randomized 1:1 to either aerobic exercise training (intervention group, *n* = 15) or no intervention (“do-as-usual” control group, *n* = 15). See Fig. 1 for the study design. The trial will be reported using the CONSORT extension for non-pharmacological treatment interventions [47] and key elements from the REPORT Trial guide [48].

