## Statistical methods

### Statistical methods for primary and secondary outcomes {20a}

#### Analysis methods

The primary outcome (fat fraction) will be analyzed using a per protocol analysis according to the predefined compliance criteria. In addition, an intention to treat analysis will be carried out for all participants including those with low compliance. For both analyses, to detect if there is a significant change in liver fat fraction between the intervention and control group, analysis of covariance (ANCOVA) will be used including age, sex, and BMI as covariates. The estimated difference in mean change from baseline to end of the trial between the intervention and control group will be reported together with 95% confidence intervals and *p*-values.

Continuous secondary outcomes will be analyzed using ANCOVA with the same adjustments as for the primary outcome. Estimated differences in mean from baseline to end of the trial between the intervention and control group will be reported together with 95% confidence intervals and *p*-values. Model fit will be evaluated using graphical methods such as residual and QQ plots and, if necessary, outcomes will be log-transformed. For log-transformed outcomes, results will be back-transformed accordingly.

Statistical analyses will be carried out using R (R Core Team, 2021). R: A language and environment for statistical computing. R Foundation for Statistical Computing, Vienna, Austria. URL https://www.R-project.org/.

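### The stated inputs at one-sided 0.05 give 11 or 12 per group, not 14, and the one-sided test does not match the 95% confidence intervals to be reported

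*Protocol article*

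**What the plan says.** Sample size {14} of the protocol article sets out the calculation for the primary outcome, the liver fat fraction measured by MRI.

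- **Sidedness.** The choice is deliberate and a reason is given: "The one-sided test is chosen due to the current literature", which the authors read as showing that exercise lowers liver fat and does not raise it.
- **Inputs.** "Assuming a SD of − 2,6 [36" gives the SD with a minus sign, and the control arm is assumed to show "no change in the control group".
- **Target.** The text states that 80% power to detect a 2.8-point "between-group change in liver fat fraction with a one-sided 0.05 significance requires" 14 in each group.

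Trial design {8} plans 15 per group. No dropout rate is stated.

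Analysis methods, under section {20a}, plans an ANCOVA. The estimated difference in mean change "between the intervention and control group will be reported together with 95% confidence intervals" and p-values. That section does not mention a one-sided test, a one-sided bound or a 90% interval.

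**The concern.** Two things do not fit together.

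First, a standardised difference slightly above 1, tested one-sided at 0.05 with 80% power, should need fewer than 14 per group. If so, the printed n, power and significance level cannot all be right, and a reader cannot tell what power the trial was built to have.

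Second, the sample size section tests one-sided at 0.05, while the analysis section reports intervals that on their usual reading match a two-sided 0.05 test. A primary result could then be called significant under one section while the interval required by the other includes zero. The section on blinding {17a} accepts that the primary investigator may carry out the analysis unblinded, so the rule should be fixed beforehand.

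**Working it through.** **Inputs, all from Sample size {14}:** difference 2.8 points; SD 2.6 (absolute value, since an SD cannot be negative); power 80%; alpha 0.05 one-sided; equal groups.

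**Step 1: try to reproduce 14 under the stated rule.** The normal approximation is n per group = 2 × (z_alpha + z_beta)² × (SD/difference)², with (2.6/2.8)² = 0.862.

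- One-sided 0.05: 2 × (1.645 + 0.842)² × 0.862 = 10.66, so 11 per group.
- One-sided 0.05 by noncentral t (standardised difference 2.8/2.6 = 1.077): 11.40, so 12 per group. Power is 78.6% with 11 and 81.9% with 12.

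The stated 14 is not reproduced. The total would be 22 to 24, against the 28 that 14 per group implies.

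**Step 2: the same inputs, two-sided.**

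- Normal approximation: 2 × (1.960 + 0.842)² × 0.862 = 13.54, so 14 per group.
- Noncentral t: 14.56, so 15 per group.

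**Step 3: power by t-test at the relevant group sizes.**

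| Evaluable per group | One-sided 0.05 | Two-sided 0.05 |
|---|---|---|
| 13 | 84.7% | 75.0% |
| 14 | 87.1% | 78.3% |
| 15 | 89.1% | 81.2% |

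By the normal approximation, power with 14 per group is 88.6% one-sided and 81.3% two-sided.

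**Step 4: where the two rules disagree, at 14 per group.** The standard error of the difference is 2.6 × √(2/14) = 0.983, with 26 degrees of freedom.

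- Smallest reduction significant at one-sided 0.05: 1.706 × 0.983 = 1.68 points.
- Smallest reduction whose 95% confidence interval excludes zero: 2.056 × 0.983 = 2.02 points.

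An observed reduction between these values passes the one-sided test while its 95% interval includes zero. Under the planned effect the probability of this is 87.1% − 78.3% = 8.8 percentage points, or about 9% of trials.

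**Step 5: other routes to 14.**

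- Twelve per group inflated for 10% loss gives 12/0.9 = 13.3, so 14.
- One-sided 0.05 with an SD of about 2.9 gives 13.99 by t-test, so 14.

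Neither the loss rate nor that SD is stated in the document.

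**The case against.** The best defence is that nobody is harmed. Under the rule the protocol states, 14 per group has more power than claimed, and 15 are planned. That stands: the error is conservative, and it gives no ground for enlarging the trial or calling it underpowered under its own rule.

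It can also be said that a prespecified one-sided test with a stated reason, in a trial labelled exploratory, is legitimate, and that the analysis section never uses the word two-sided. Both are true. The one-sided choice is not itself the error. A reader might go further and say that the success rule is undefined. The document does not support that, because a rule is stated; it is inconsistent with the interval to be reported, on the ordinary reading of a 95% confidence interval. Nor does the direction of the result depend on which rule is used; only its significance does.

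A reader might also infer that n was computed two-sided and then described as one-sided. The match at 14 holds only for the normal approximation, and step 5 gives two other routes. None of the three is documented, so the cause remains open.

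Finally, the minus sign on the SD might suggest that a mean change was entered as the SD. The cited source is not at hand, and on the page this is only an impossible sign. It justifies a check, not a conclusion.

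The missing analysis plan does not remove the point. The article prints a figure that its own inputs do not give, and it pairs a one-sided test with an interval of a different level.

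**Conclusion.** The point holds in a limited form. With the stated inputs, 14 per group is wrong for 80% power at one-sided 0.05: the answer is 11 or 12, and the power at 14 is about 87%. This part is arithmetic and is certain, given an SD of 2.6.

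The sidedness mismatch between the two sections is real on the conventional reading of a 95% interval. It affects observed reductions of 1.68 to 2.02 points at 14 per group, about 9% of trials if the planned effect is true. Those figures assume a two-sample comparison of changes with SD 2.6; they ignore the small effect on degrees of freedom, and any gain in precision, from the age, sex and BMI covariates.

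If the two-sided reading is adopted, the margin is thin. The analysis named first for the primary outcome is per protocol, and missing data will not be imputed (section {20c}), so fewer than 15 per group may be evaluable. With 14, two-sided power is already below 80% by t-test.

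**What to change.** Restate the calculation so that sidedness, n and power agree, and apply the same rule in Sample size {14} and in Analysis methods. Do this before the analysis. It changes or clarifies the primary significance rule of a recruiting trial, so it should go through the amendment route in section {25} and not be treated as an editorial correction.

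- **Simplest choice: two-sided 0.05 with the 95% confidence interval.** Name the method of calculation and state t-test power of 81% with 15 evaluable per group, 78% with 14 and 75% with 13. The planned 30 participants stay. The cost is a stricter significance rule.
- **If the one-sided 0.05 test is kept:** state 12 per group as the requirement, or 87% power at 14 and 89% at 15. Report a matching 90% confidence interval or a one-sided 95% bound for the primary outcome.

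In either case, print the SD without the minus sign and confirm against the cited source that 2.6 is an SD of change. If it is not, the power figures must be recalculated.

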### Recruitment {15}

The participants will be recruited through the outpatient clinic at the Department of Infectious Diseases, Copenhagen University Hospital, Hvidovre, at the Department of Infectious Diseases, Copenhagen University Hospital, Rigshospitalet, at the Department of Gastroenterology, Copenhagen University Hospital, Herlev, and through recruitment postings. Eligible participants will be identified by the primary investigator, who will contact the clinical staff treating the patient, who will request if the participants would like to receive information about the trial from the primary investigator. The recruitment postings will be posted in newspapers, through patient associations, on social media, by posters, and by flyers in local areas and hospital departments. Interested persons who have seen the recruitment postings can then contact the primary investigators by either email or phone. When including participants, the participants will receive a written and oral presentation of the trial in a closed environment without disturbances and the option for asking in-depth questions. The information will be given by the principal investigator. The trial participants will be given time—up to 2 weeks—to consider if they are willing to participate. If requested, an assessor can participate and ask questions to the primary investigator, including the trial participants. Inclusion will require written consent from trial participants before enrolment in the trial.

The flow chart of the trial will follow the CONSORT guidelines and will include the number of participants who (a) received written material and oral information about the trial, (b) were assessed for eligibility at prescreening, (c) were included in the trial, (d) attended CAP screening, (e) were randomized, and (f) were allocated to the two groups (intervention/control).

## Assignment of interventions: allocation

### Sequence generation {16a}

Randomization 1:1 is done using https://www.sealedenvelope.com/simple-randomiser/v1/lists with varying block randomization. No stratification is used.

### Concealment mechanism {16b}

Sealed envelopes with randomization intervention (1) or no intervention (0) will be made beforehand for the included trial participants by an outsider and investigators will not have knowledge of the content of the envelopes. The envelopes are sequentially numbered, opaque, sealed envelopes. The envelopes are opened sequentially, and each envelope will be irreversibly assigned to the participant after their first visit. Patients are given ID numbers accordingly to the time they have their first planned trial visit, e.g., FL01, FL02.

### Implementation {16c}

The randomization will be done according to the sealedenvelope.com algorithm, the participants will be enrolled after an outpatient visit, and on the first possible following day, the participants will show up for the informed consent. The primary investigator will open the sealed envelope at the end of the baseline examinations.

## Assignment of interventions: blinding

### Who will be blinded {17a}

We will strive to achieve blinded assessment of primary outcome and data analysis, but currently, due to limited funds, the primary investigator might be the one to assess the outcomes and make the data analysis and are unfortunately unblinded. If we do not succeed with the blinded assessment of outcome and data analysis, it will be described transparently in the trial report.

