### Procedure for unblinding if needed {17b}

Not applicable, since there is no blinding of investigators during the trial and the blinding is intended only for the assessment of primary outcome and data analysis.

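### Masked reading of the primary MRI outcome and masked analysis are only an aspiration: the fallback lets the person who opens the envelopes do both unblinded, with disclosure as the sole remedy

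*Protocol article*

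**What the plan says.** Who will be blinded {17a} states an aim: "We will strive to achieve blinded assessment of primary outcome and data analysis". The same sentence qualifies it, "but currently, due to limited funds", and continues that "the primary investigator might be the one to assess the outcomes and make the data analysis", adding that this person is unblinded. The fallback is reporting: "If we do not succeed with the blinded assessment of outcome and data analysis, it will be described transparently in the trial report".

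Implementation {16c} settles what this person knows: "The primary investigator will open the sealed envelope at the end of the baseline examinations". Procedure for unblinding {17b} confirms that investigators are not blinded during the trial and that "the blinding is intended only for the assessment of primary outcome and data analysis".

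Outcomes {12} defines the primary outcome as the MRI proton density fat fraction of the liver at week 13, and names the scanner and sequence. The article describes no coding of scans, no separate reader and no masked group labels.

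**The concern.** The trial compares supervised cycling with no intervention, so participants and trainers know the allocation. Masked reading and masked analysis are the two points at which the plan itself wants blinding, and it makes both optional. The person who may carry them out holds every allocation and also contacts exercisers who miss or do not comply with sessions (Motivation strategies; Strategies to improve adherence {11c}). The plan also expects a direction: the primary hypothesis is that exercise lowers liver fat, and Sample size {14} uses a one-sided test for that reason.

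If the reading involves any judgement, an unmasked reader with that expectation could shift the difference between arms. An unmasked analyst could be influenced when deciding who belongs in the analysis set. Describing this afterwards leaves the estimate as it is.

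**Working it through.** **Reading the sections together**

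1. Implementation {16c}: the primary investigator opens each envelope after the baseline examinations and therefore knows every arm.
2. Who will be blinded {17a}: the same role may assess the outcomes and analyse the data, unblinded.
3. Procedure for unblinding {17b}: these two steps are the only ones at which blinding is intended. If the aim in {17a} is missed, no masked step remains.
4. The reason given is money, as though masking required another assessor. What it requires is that the reader cannot link a scan to a person, visit or arm. One reader can work from coded scans if somebody else holds the key.
5. Suitable key-holders already appear in the plan. Concealment mechanism {16b} has an outsider prepare the envelopes, and Plans for assessment and collection of outcomes {18a} has two people enter the data.
6. The primary comparison needs 30 participants × 2 scans = 60 scans if all are completed.
7. Two features limit what relabelling alone can do. Data management {19} says MRI results also appear in the patient files, where they are identifiable. The per-protocol set depends on session attendance and heart rate (Analysis methods; section {20c}), so exclusions for non-compliance fall only in the exercise arm and can reveal it even when arms are labelled A and B.

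**Size, by assumption**

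The documents give no figure for reader bias, so there is none to reproduce. Inputs from the plan are SD 2.6 percentage points and target difference 2.8 (Sample size {14}), and 15 per arm (Trial design {8}). The differential shift b is assumed.

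- Standard error of the difference = SD × √(2/n) = 2.6 × √(2/15) = 0.95
- b = 0.25: 0.25/0.95 = 26% of the standard error; 0.25/2.8 = 9% of the target
- b = 0.5: 0.5/0.95 = 53% of the standard error; 0.5/2.8 = 18% of the target

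The next table gives the chance of declaring a benefit when there is none, from a two-sample t-test with 15 per arm, SD 2.6 and a noncentral t distribution:

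| Assumed shift favouring exercise | One-sided 5% test | Favourable 2.5% tail of a two-sided test |
|---|---|---|
| 0.25 | 8% | 4% |
| 0.5 | 13% | 7% |
| 1.0 | 27% | 17% |

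A smaller per-protocol set would have a larger standard error and so slightly lower ratios. With 14 per arm, 2.6 × √(2/14) = 0.98, and the same shifts are 25% and 51% of it.

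**The case against.** The plan is candid. It states the aim to blind, names the obstacle and promises transparency. Nothing is contradicted, and a reader should not infer that unblinded reading is certain or that the authors are indifferent to it. This stands, but the text still permits the weaker course.

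The amount of reader discretion is unknown. The outcome is a quantitative imaging measure, the scans are done in a radiology department, and the article does not say who produces the value or how the liver is sampled. A condensed article may leave that to the full protocol. So bias is possible, not shown.

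Some stronger readings are tempting and are not supported:

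- *Masking is the only protection left.* Envelopes are prepared by an outsider, allocation follows the baseline examinations, data are entered twice, and the outcome is not self-reported. None of these replaces masked reading, but they are protections.
- *An unblinded analyst may choose the transformation of the primary outcome.* The sentence "Model fit will be evaluated using graphical methods such as residual and QQ plots", with the log-transformation option, stands in the paragraph on continuous secondary outcomes. For the primary outcome the article names ANCOVA with age, sex and BMI.
- *Masking would cost almost nothing.* The documents give no costs. That the work is modest is a judgement from the number of scans, and the outsider's continued availability is not stated.

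Finally, A/B labels may not mask this analyst, for the reason in step 7 of the working, and the investigator knows the participants. That objection is right and shapes the fix.

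**Conclusion.** The point holds as one of commitment. The plan makes masked reading and masked analysis optional and allows the person who knows every allocation to do both. Disclosure does not remove observer bias, and lack of funds for another assessor is not a sufficient reason, because a second reader is not needed.

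The size cannot be established from the documents. The figures of 26–53% of the standard error rest on an assumed shift of 0.25 to 0.5 points, the plan's SD and full arms of 15. They show that a shift small beside the 2.8-point target would matter in a trial of this size; they do not show that one will occur. The conclusion rests on the text and not on these figures.

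**What to change.** In Who will be blinded {17a}, replace the aspiration with a fixed procedure:

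- Export baseline and week-13 scans under random codes, with ID, date, visit and arm removed. Shuffle them and read them in one batch after the last week-13 scan.
- Take the research value only from the coded exports, not from the result in the patient file.
- Give the key to someone other than the reader, such as the outsider who prepared the envelopes or a data-entry person.
- Fix the per-protocol set from the exercise records before outcome data are linked.
- Lock the model specification before arm labels are attached. Use A/B coding as an added safeguard only.
- Keep the promise to report any step that was not masked.

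The cost is some relabelling work and a delayed research read, with no extra reader or scan. Clinical reading for incidental findings can go on as now. Trial status reports 13 patients recruited by January 2023, so some scans may already have been seen. They can still join the coded batch, but their masking will be incomplete and the report should say so.
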